#### Equal energy expenditure fashion and conditions

Energy expenditure by activity will be estimated through metabolic equivalents (METs) which is defined as the amount of oxygen consumed while sitting at rest, and it represents a practical way of expressing the energy cost of physical activities as a multiple of the basal metabolic rate (BMR) [93]. As estimation of METs strongly depend on body weight the following equation will be applied with the intention to personalize the total energy cost to each participant: Total Energy Cost (kcal) = METs x BMR (kcal/min) x duration (min), where the BMR for boys between 10 and 18 years is predicted using the equations: BMR (kcal/min) = [17.686 x weight (kg) + 658.2]/1440 [94].

According to the last “Youth Compendium of Physical Activities” [95] children above 10 years spend 1.3 METs sitting “watching TV” (similar to sitting in school) as Sedentary condition (SC), while that in a “walk self-paced brisk” as the Moderate-Intensity Continuous Training (MICT) protocol they will spend 5.0 METs, and for a vigorous PA such as “obstacle/locomotor course–vigorous” exercise as a Cooperative High-Intensity Interval Training (C-HIIT) they will spend 8.6 METs. In this sense, SC will be the referential group, and then both MICT and C-HIIT will have the same energy cost that SC.

Finally, to confirm children’s physical intensity each one will use a heart rate monitor (Polar H10) to encourage maintenance of the appropriate exercise intensity, which will be connected to an iPad or mobile application (Polar Team).

#### Characteristics of each PA protocol

##### SC

Each adolescent will be seat in a room within the laboratory with a TV in front of. They will watch a documentary about nature during around 90 min because in Chile any traditional academic subject as math or language last this time. Temperature, light, and sound of the room will be controlled.

##### MICT

Each adolescent, together with a personal trainer of our team will go for a walk self-paced brisk. This PA will be performed outdoor because is more realistic to school activities. The MICT protocol must be done to moderate intensity, corresponding to 60% of heart rate maximum [82].

##### C-HIIT

Each adolescent together a personal trainer will do a circuit training based on a collaborative fashion. The specific protocol has been published previously [92]; in brief, it consists in four series of four cooperative exercises which combining cardiorespiratory, speed–agility, and coordinative training exercises because these are the fitness components that mostly enhance cognitive capacity in adolescents [56, 92, 96]. The session will be organized with work-to-rest ratios of 20:40 s. Both, MICT and C-HIIT protocols include a short 4 min warm-up (running, sideways movements and dynamic stretching at medium intensity) and 4 min of cool-down. The C-HIIT protocol must be done to high intensity, corresponding to ≥85% of maximum heart rate [97].

After each PA protocol, the participants will undergo EEG and eye-tracking measurements as follows: 1st, resting state spontaneous brain activity will be assessed during 3 min with EEG only, and subsequently, eye-tracking will be registered in parallel with EEG while participants perform the cognitive tasks (a working memory task and a reading task). The measurements will start between 20 to 25 min after the end of each condition. In this way, we will emulate a school recess in the Chilean context, before the start of the next subject. All measures will be carried out in the “Laboratorio Lenguaje & Cognición ELV”, which belongs to the Literature and Language Sciences Institute of the Pontificia Universidad Católica de Valparaíso. To avoid subjective influence of evaluator, when the participants go to the laboratory, the evaluator will be blinded according to which PA protocol participants performed.

Regarding optimize participant retention, parents or legal guardian will be contacted and reminder by phone calls, or email when the participant loses any of the three scheduled sessions. Then, missed sessions will be reprogramed according to availability of participants and respecting study design. An inventory of each section of this trial is available in the SPIRIT checklist (Additional file 1).

### Neuroelectric and eye-tracker measurements

#### EEG measurement

A B-Alert X24 device for EEG (Advanced Brain Monitoring, California, United States) will be used, which consists of 24 active electrodes that minimize the noise of electrical devices outside the biological processes of interest, ensuring good signal quality. Two channels will be used to register electrooculographic activity, to better discriminate between true electroencephalographic and electrooculographic activity associated with eye movement and blinking. Recordings will be done at a sampling rate of 256 values per second, with a band-pass filter between 0.1–100 Hz, and a notch filter of 50 Hz to eliminate the noise of the surrounding alternating current in the room. It should be noted that this equipment is wireless, which makes it more convenient and faster to mount on participants.

#### Eye-tracker

A Tobii Pro TX300 (Tobii, Stockholm, Sweden) will be used to track eye movements directly through a light sensitive camera near the infrared spectrum. This equipment studies the visuomotor characteristics during the process of reading and the trajectories of the look around each word. In addition, it will serve to define the exact moments at which these words are read and thus be able to synchronize the EEG record to calculate an average signal (N400) that reflects the brain’s processing of language. The same device records raw values of pupil size (diameter), saving all data with a sampling rate of 300 Hz.

Specific software of each company will be used for the registration of the EEG and eye-tracker signals, synchronized through digital pulses sent via a parallel port, from the PC housing the stimuli presentation software. This will allow having a single timeline for both registers. The data will be analyzed through analysis packages and custom scripts written in Matlab. For the spectral analysis of EEG during the recording at rest condition, the EEG signals will be filtered between 7 and 13 Hz, and the Hilbert transform method will be applied, which allows calculating accurately and without restrictions of precision both the dominant frequency and the oscillatory amplitude of a frequency band. This method has not been applied before in this line of research, and has several benefits with respect to conventional spectral methods such as the Fourier method. Then, the results of each channel will be averaged to have a more robust overall measurement of the peak of the alpha wave, and its amplitude changes when opening / closing the eyes. For the cognitive tasks (working memory and reading), the amplitude and latency of the corresponding event related potentials will be quantified (P300 and N400, respectively).

### Cognitive tasks during neuroelectric and eye-tracker measurements

#### Working memory task

A N-back task will be run through E-Prime 2.0 software synchronized with the electroencephalographic recording system and the eye-tracker, to measure neuroelectric activity and pupil size diameter time-locked to the presentation of each stimulus (targets and non-targets). The protocol is very similar to the one previously explained for the 0-back and 2-back conditions during fMRI assessment. The main difference of the present task with respect to the fMRI’s N-back task is that children must press in the keyboard the number “1” when they detect a target stimulus or the number “2” for non-targets. This type of task generates an EEG potential related to cognitive processing, characterized by a positive deflection that peaks roughly around 300 ms (P300), which has been widely studied in various types of tasks that require conscious attention, in any perceptual modality [98, 99]. In other words, it is a potential related to events that are consciously perceived, which does not depend on the stimulated perceptual path, but rather on the need to reallocate cognitive resources and develop appropriate responses according to the ever-changing context. To isolate the EEG patterns of P300 in working memory, we will subtract to the result of a 2-back task, the one of a 0-back. The P300 event-related potential is expected to emerge especially in the average EEG signal time-locked to the onset of detected targets stimuli [100, 101]. Artifacts such as electrooculographic signals will be subtracted from the data with an algorithm implemented in EEGLAB [102], an EEG analysis toolbox running in MATLAB (Mathworks®). Manual rejection of single trials will be considered based on visual inspection of artifacts in data.

#### Reading task

Language processing will be assessed by a reading comprehension task where short paragraphs will be presented to be read normally. The eye-tracking technique will be employed to record eye position, movement and pupil diameter, simultaneous to the EEG record. Participants will seat in front of a monitor, at approximately 60 cm, placing their chin on an ergonomic stand piece, which helps to decrease head movements and improves eye-tracker signal precision. The reading task will be presented with the latest version of Tobii Pro Lab. After calibrating the system, each child is given a brief contextualization of the topic, before they start to read, knowing that later they will be asked seven comprehension questions with varying degrees of complexity. The participants must indicate the correct answer among four alternatives. It should be noted that three literary texts will be used, presented in a random fashion (1 per exercise condition). These texts will have the same difficulty, the same distribution of areas of interest, similar amount of words, and will be previously validated by a panel of experts. The reading of each word is expected to generate an EEG negative potential with latency close to 400 ms (N400). The amplitude, topographic distribution and latency of this potential are electrophysiological neuromarkers of linguistic ability in general, and the ability to construct meaning from words [103]. The eye-tracker will be used to study the ocular trajectory during reading and establish the moments when words are read. EEG and eye-tracking will be registered simultaneously to record eye movements related to reading, giving measures such as reading speed, fixation durations, number of fixations, among others), and to measure eye fixation related EEG potentials associated with cognitive load while reading words [50]. The reader should note that this potential coincides experimentally with the N400, so they may represent different brain processes superimposed, or be essentially the reflection of the same mechanism.

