##### Total sample size and power

For feasibility reasons, the school chosen for the development of exercise sessions is close to our laboratory. Sample size is estimated according to the mean difference of two independent samples from a randomized controlled trial were a working memory task (2-back) was tested [56]. Children control group achieved a positive variation (∆ = 2.05 ms; SD = 93.1) while exercise group a negative variation (∆ = − 69.45 ms; SD = 91.6) [56]. A loss rate of 20% was considered. Statistical power analysis indicated that at least 32 participants would yield adequate power (i.e., > 80%) and α (i.e., < 0.05), with a detectable variation of 71.50 ms (∆ between experimental conditions – control condition).

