### Design of cross-over acute trial

The design of the second part of the project will consist of a cross-over trial where the participants will perform, on different days, three different PA protocols with equal energy expenditure fashion in a random order. Before starting this part, schoolchildren will be evaluated by a physician (preparticipation physical evaluation), under previous authorization of their parents. The examination will consist in the realization of a complete clinical history and a general physical examination, with the purpose of verifying their health status and avoiding possible injuries or illnesses during PA protocols. Any adverse events occurring during the trial will be documented and submitted to the physician, which will analyze the exclusion of the participant from the trial.

Each child will visit our laboratory three times, every 2 weeks to ensure a “wash-out” period with the purpose of mitigating the PA effect from each protocol. The order will be determined using a computer-generated ordering system. The random sequence was generated by the web-based Research Randomizer (randomizer.org). A staff member responsible for recruitment will perform randomization. Participants will assist to the three different sessions at the same weekday (e.g., Monday) and at the same daytime to avoid differences in preceding school activities or circadian rhythms [82]. Participants will undergo a “Sedentary condition” (SC), sitting and watching a documentary on TV as has been used previously [82], and two different PA protocols consisting in “Moderate-Intensity Continuous Training” (MICT), continuous outdoor brisk walking/running; and “Cooperative High-Intensity Interval Training” (C-HIIT), composed of a circuit training with a partner (physical education teacher) (Fig. 1). These three protocols have been chosen in view of what corresponds to types of activities usually performed in schools. Thus, SC mimics the time spent during any academic lesson (i.e. mathematics or language lessons); MICT represents the typical activity in a PE class; and C-HIIT has been selected since it is postulated as an exercise protocol that could possibly be implemented in thethe PE class [92]. The three protocols are designed so that energy expenditure is equivalent between them, to eliminate differences in the energy expenditure as a possible confounding factor. Thus, the duration will be different among protocols.

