#### Reading task

Seven questions with varying degree of comprehension complexity will be given after the texts are read. For every question there will be four alternatives to choose as the correct answer.

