##### N400

This linguistics-related event-related potential also will be described according to latency and amplitude. Because it will be synchronized with the eye fixation on words during the reading task, it is conceptually a type of fixation-related potential.

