#### Cross-over study

Differences among condition will be calculated using general lineal models (95% confidence) and estimating the Hedges effect size [115]. Strength of effect will be assessed according to the following interpretation: trivial (0–0.19), small (0.20–0.49), medium (0.50–0.79) and large (0.80 and greater) [116]. The significance threshold analyses will be *p* < 0.05.Regarding missing data, it is anticipated that missing data could be due to faults in the EEG and eye-tracker, and thus will be missing at random. For this reason, multiple imputation will be used to address this issue.

In addition to performance in the task of working memory and reading, several neurocognitive variables (amplitude and latency of both potentials, frequency of the alpha wave, and variation of its amplitude with the opening of the eyes) will be studied statistically using a model of mixed effects, which initially will use the factors: subject, exercise protocol and cognitive ability (high or low performer). Subsequently, it will be extended to other factors (the rest of the measures of the Cogni-Action Project, such as body composition, sexual development status, anthropometric measures, socioeconomic, brain structure, etc.), to establish which factors and interaction between them have greater statistical significance in the acute effects of PA on cognitive and academic performance.

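### Reading texts are randomised without balancing over conditions and text is not a model factor: a small, avoidable loss of precision in the reading-task contrasts

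*Protocol article*

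**What the plan says.** The Reading task section, under the cognitive tasks of the cross-over study, says that "three literary texts will be used, presented in a random fashion (1 per exercise condition". It then describes a control on text differences: "These texts will have the same difficulty, the same distribution of areas of interest, similar amount of words, and will be previously validated by a" group of experts. The order of conditions is also random; in Design of cross-over acute trial, "The order will be determined using a computer-generated ordering system". Neither place says that texts are balanced over conditions or sessions.

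The Data analysis plan for the cross-over study describes a mixed-effects model, "which initially will use the factors: subject, exercise protocol and cognitive ability (high or low performer". It continues: "Subsequently, it will be extended to other factors (the rest of the measures of the Cogni-Action Project". The examples it gives for that extension are characteristics of the participant, such as body composition, pubertal status and socioeconomic position. Text is in neither list.

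Several primary outcomes of the cross-over study come from the text read:
- Comprehension: "Seven questions with varying degree of comprehension complexity will be given after the texts are read".
- N400: "it will be synchronized with the eye fixation on words during the reading task".
- Word fixation times.
- The pupil-based index, as far as it is taken during reading.

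**The concern.** These outcomes depend on which words and which questions a boy was given. With three texts and three conditions, every comparison of two conditions within a boy is also a comparison of two texts. If the texts differ at all, part of that comparison is text rather than exercise. Simple random allocation makes this part average out to zero, but in one trial of 32 boys it does not cancel exactly. A model without text leaves its variance in the error term.

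What is at stake is precision on the reading-task outcomes. The text given in each session is known, so the loss can be avoided.

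**Working it through.** **The plan's own figure.** The article gives no sample-size calculation for reading. Its 32 rests on 2-back response time: difference 71.50 ms, SDs 93.1 and 91.6, pooled SD √((93.1² + 91.6²)/2) = 92.35. With two-sided 5% and 80% power, 2 × (92.35 × (1.960 + 0.842)/71.5)² = 26.19 per group. Adding 20% gives 26.19 × 1.2 = 31.4, so 32. That agrees with the plan. Only the number of boys is used below.

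**Assumption.** The article gives no size for text differences. Let D be the gap between the easiest and hardest text in within-boy SDs, with text effects −D/2, 0 and +D/2. D is taken as 0.25, 0.5 and 1.0.

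**Formula.** Each boy reads all three texts, in random order over conditions.
1. The two texts in a condition contrast are drawn without replacement. Their difference has mean 0 and mean square (D²/4 + D²/4 + D²)/3 = D²/2.
2. The error variance of a within-boy difference is 1 + 1 = 2.
3. With text not modelled, the contrast variance over 32 boys is (2 + D²/2)/32 = 0.0625 + D²/64.
4. The relative rise in variance is (D²/2)/2 = D²/4. It does not depend on the number of boys.
5. The SD of the chance text shift is √(D²/64) = D/8. Its square is the second term in step 3, so the shift and the variance rise are the same quantity and must not be added together.

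| D | Variance rise | SE (0.25 without text differences) | SE rise | SD of chance shift |
|---|---|---|---|---|
| 0.25 | 1.6% | 0.252 | 0.8% | 0.031 |
| 0.5 | 6.25% | 0.258 | 3.1% | 0.0625 |
| 1.0 | 25% | 0.280 | 11.8% | 0.125 |

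In terms of boys, 32/1.0625 = 30.1 and 32/1.25 = 25.6. The loss equals about 2 boys at D = 0.5 and about 6 at D = 1.0.

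**Simulation.** 32 boys, no condition effect, 6,000 runs, paired test with text ignored.
- Random text per boy: the mean contrast is within 0.005 SD of zero. The SEs are 0.254, 0.261 and 0.278, which match the formula within simulation error. The type I error is 4.9%, 5.2% and 4.7%.
- Chance imbalance: 32/3 = 10.7 boys are expected in each of the nine text-by-condition cells. On average the largest cell holds 14.6 and the smallest 6.9.
- Balanced text, still not modelled: at D = 1.0 the SE returns to about 0.25, but the type I error falls to 3.4%. The estimate is more precise, but the test does not see it, because text variance is still in the estimated error. Balancing and a text term therefore do different work, and both are needed.

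**The case against.** The strongest reply is that random allocation of matched texts is already a sound design. The article states equal difficulty, the same layout of areas of interest and similar length, with expert review beforehand. If the matching works, D is small and the loss is about 1% in the standard error. The factor list is called initial, and an analysis plan that is not shown may contain a text term.

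Most of this stands, and it is why the point is minor. It does not remove the point. The article states both an allocation method and a factor list, and the extension it describes runs to participant measures. The matching is a planned property of the texts, and the sentence does not mention the question sets. With seven questions, one harder item moves a score by 1/7. The article does not say what the expert validation rests on, so nothing can be inferred about D in either direction.

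A reader might also infer something much stronger: that one text is tied to each condition, so that text and condition are confounded. The full gap D would then enter a contrast as bias, and the simulated type I error would be 17%, 49% and 97% at D = 0.25, 0.5 and 1.0. The article does not support this. Giving every boy the same text after the same condition would not be presenting texts at random. The parenthesis most naturally means that each boy reads one text per session. It could be worded more tightly, but it is not evidence of confounding.

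**Conclusion.** The point holds as a minor loss of efficiency. Text is randomised without stated balancing and is not named in the model, so text differences that survive the matching stay in the error of the comprehension, fixation, N400 and reading-pupil contrasts. There is no systematic bias and no inflation of the type I error. For an easiest-to-hardest gap of 0.25 to 1.0 within-boy SD, the standard error of a contrast rises by about 1% to 12%.

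This rests on three assumptions: text is randomised per boy, the three text effects are evenly spaced, and the assumed range of D applies. The working memory and resting EEG outcomes are not affected.

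**What to change.** In the Reading task section, state that text is assigned per boy, counterbalanced over condition and session as equally as 32 boys allow, and generated together with the condition order. This also rules out a text fixed to a condition. One workable form is a block of six sequences made of two 3 × 3 Graeco-Latin squares. Since 32 = 5 × 6 + 2, each text-by-condition cell can then hold 10 or 11 boys.

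In the cross-over analysis plan, add text as a fixed factor for all reading-task outcomes: comprehension score, fixation times, N400, and the pupil index during reading. If the order list is already in use, the text term can still be added, provided the text read in each session is recorded.

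The cost is one column in the randomisation list and 2 degrees of freedom. With complete data and subject and protocol in the model, the residual falls from 96 − 1 − 31 − 2 = 62 to 60. No extra data are needed.
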